#### Case identification and recruitment

Patients will be enrolled by the principal investigator, the coordinating investigator or the research nurse of the Erasmus Medical Center, after signed informed consent was obtained at one of the participating centres. Patients will be informed by their primary clinician (gynaecologist) and provided with a patient information brochure. If the patient is interested in participating, a hardcopy informed consent form is provided or a link to ValidSign^21^ via email will be sent, where a special PDF version of the informed consent form is available. The participant can sign this with an ‘advanced electronic signature’ with SMS verification. The digital consent form will then be downloaded to a secure drive on the Erasmus MC network for archiving. From all participants who provided written informed consent in a participating centre, the signed form will be scanned and stored digitally in the participating centre. All clinical data are prospectively collected through electronic case report forms (e-CRF) by the treating gynaecologist of the participating centre. The coordinating investigator will re-evaluate the provided data and ensure that collecting data is complete. All participants will receive an online questionnaire using a survey package in Castor Electronic Data Capture (EDC) at the time of diagnosis and during follow-up after 6 months, 2 years and 5 years of diagnosis, respectively. The survey package includes three online questionnaires: EQ-5D-5L QOL, QLQ-EN24 and QOL-C30. The estimated time needed to complete the three questionnaires is 15 min. Regarding therapy of SEIC, all treatment options are allowed (surgery, systemic therapy, radiotherapy). There will be no specific, patient-tailored recommendations regarding the given therapy. All interventions are part of regular medical treatment and are registered. The methods are all part of standard clinical care, apart from the collection of data through the questionnaires. Since this is an observational study, no interventions are performed.

#### Sample size calculation

A formal sample size or power calculation was not performed because this study is designed as a prospective registry of a rare disease rather than a hypothesis-testing clinical trial. The primary objective is to establish a comprehensive longitudinal registry and include as many eligible patients as possible to improve understanding of this rare disease entity. In a previously cited retrospective study conducted in the Netherlands, 23 patients were diagnosed with SEIC over an 8-year period (2012–2020).^20^ The Netherlands Comprehensive Cancer Organisation (IKNL) registered 77 patients with SEIC between 2015 and 2025. We estimate that more patients may be diagnosed in the coming years due to increased awareness among gynaecologists and pathologists and improved recognition of the disease entity. Additionally, increased awareness may lead to more frequent resection of endometrial polyps and subsequent diagnosis of SEIC. Therefore, we anticipate approximately 100 eligible patients in the Netherlands, of whom approximately 75% may consent to participate in the registry. Participation of centres outside the Netherlands is expected to further increase the number of eligible patients. The aim is to include all eligible patients diagnosed during the study period to maximise the completeness of data collection and improve the precision of descriptive estimates. Data generated through this registry are expected to support future hypothesis-driven studies and inform clinical management of this rare disease entity.

### Outcomes

#### Primary and secondary outcome

The primary outcome is PFS, defined as the time from histopathological diagnosis of the lesion to the first occurrence of disease progression, recurrence or death from any cause, whichever occurs first. Disease progression or recurrence is defined as radiologically, histologically, or clinically documented local, regional or distant disease. Patients without an event will be censored at the date of last follow-up. Secondary outcomes include overall survival (OS), disease-related symptoms, health-related QoL, type and extent of surgical and adjuvant treatment, severe postoperative complications (Clavien-Dindo grade III–IV), and treatment-related adverse events associated with systemic therapy or radiotherapy classified according to the Common Terminology Criteria for Adverse Events (CTCAE) version 5.0.^22
23^ OS will be defined as the time from histopathological diagnosis to death from any cause. Study outcomes/endpoints include the baseline characteristics of patients, diagnostic measurements, treatment details and follow-up data.

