19^ The impact of surgical staging on SEIC survival outcomes remains uncertain due to limited data. Lymph node sampling, especially lymph node dissection, lacks clear evidence, leaving ambiguity about SEIC metastasis to pelvic or para-aortic/paracaval nodes. Bilateral sentinel lymph node sampling has also been recommended, as sentinel lymph node procedures are increasingly performed for endometrial carcinomas.^12^ We propose that superficial intraepithelial carcinoma may disseminate via the fallopian tubes into the peritoneal cavity. Consequently, the necessity of lymph node sampling or dissection in SEIC treatment remains uncertain. In our recently published retrospective cohort study, 23 patients diagnosed with SEIC were evaluated, revealing no evidence of disease dissemination at the time of surgery. Over a follow-up period of nearly 3 years, no disease recurrences have been documented.^20^ Since complete staging did not detect any metastasis in this study it might be safe to omit standard staging procedure and to perform a simple hysterectomy with peritoneal washings and peritoneal biopsies (including biopsy of the infracolic omentum). Therefore, the primary objective of this study is to establish an international registry and longitudinally monitor patients diagnosed with SEIC, thereby contributing to the augmentation of knowledge and improvement of treatment strategies. This study establishes a registry for longitudinally monitoring of patients with non-invasive serous carcinomas/SEIC. By evaluating surgical and systemic treatments, we aim to enhance knowledge and refine treatment strategies, ultimately impacting patient survival outcomes and quality of life (QoL). Because the terminology may be further consolidated in the coming years, this study uses the combined term ‘non-invasive serous carcinoma’ including SEIC and FIGO IC serous carcinomas, and includes all lesions meeting the pathological criteria for SEIC, regardless of diagnostic nomenclature. This ensures compatibility with current and future classification systems. We hypothesise that patients with non-invasive serous carcinoma of the endometrium have a low risk of extrauterine disease and recurrence, and that less extensive surgical management may be associated with similar oncological outcomes while potentially reducing treatment-related morbidity and preserving QoL. This registry is designed to explore this hypothesis and generate evidence for future studies.

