#### Collected variables

Baseline characteristics include age, body mass index, type of physical complaints, medical history, use of medication and Eastern Cooperative Oncology Group (ECOG) performance status (known as WHO performance score).^24^ Diagnostic measurements include imaging details (date of imaging, results of gynaecological examination and advanced imaging), biochemical laboratory results and histopathology results of endometrial biopsies and surgical specimens. Regarding the histopathological examination, the following data will be obtained: the histomorphological characteristics, immunohistochemistry staining on mismatch repair proteins (MMR) and p53 mutation and results of molecular diagnostics (MSI test, p53 mutation analysis, POLE mutation analysis). Treatment details include details on the surgical treatment (date, type of surgical procedure (hysteroscopy, hysterectomy with/without salpingo-oophorectomy, staging procedure, cytoreductive surgery), perioperative findings (dissemination of disease and FIGO stage of disease), and perioperative complications) and details on administered adjuvant therapy (date, duration and type/regimen of adjuvant therapy). Given anticipated changes in FIGO and WHO terminology, all cases will be stored with raw histopathology and molecular data, allowing for retrospective reclassification according to future systems. Follow-up data will be collected at 6 months, 2 years and 5 years after diagnosis and include clinical status, symptoms, QoL, evidence of disease recurrence and disease-related or unrelated death.

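### The only surgical complication outcome stops at Clavien-Dindo grade IV, so read literally it leaves out a fatal complication (grade V)

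*Protocol article*

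**What the plan says.** All references are to the protocol article.

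- *Primary and secondary outcome* lists "severe postoperative complications (Clavien-Dindo grade III–IV" as a secondary outcome. No other outcome in that section concerns complications of surgery.
- The same section counts death in two places. PFS runs to "first occurrence of disease progression, recurrence or death from any cause, whichever occurs first", and "OS will be defined as the time from histopathological diagnosis to death from any cause".
- *Collected variables* includes, under surgical treatment, the date and type of procedure "and perioperative complications", with no limit on grade. Its follow-up items include "evidence of disease recurrence and disease-related or unrelated death".
- The *Introduction* hypothesises that less extensive surgery may give similar oncological results while "potentially reducing treatment-related morbidity and preserving QoL".
- *Statistical analysis* foresees stratifying patients by extent of surgery, on condition that subgroup analyses are feasible.

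The article nowhere mentions grade V, a range open at the top, or postoperative death as an outcome of its own.

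**The concern.** An outcome called severe complications should contain the most severe one. Here the range is written with an upper bound, and the bound falls just below death. This is more than a detail left for an analysis plan to fill in: the article states a rule, and applying the rule as written gives a wrong count whenever a complication is fatal.

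What is at stake is the attribution of harm. Morbidity from treatment is part of the registry's hypothesis, and this is the one listed outcome that records what surgery did to the patient in terms of complications. If a fatal complication falls outside it, the registry can report that a patient died but has no listed outcome that says surgery was the cause.

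**Working it through.** No figure in the article depends on this definition, and *Sample size calculation* states that no formal calculation was done. There is therefore no stated figure to reproduce. The check compares the relevant sections and then works out what one patient weighs in a proportion.

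**Where would a fatal surgical complication be counted?**

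| Place in the article | Does the death appear? | Is it attributed to surgery? |
|---|---|---|
| Severe postoperative complications, grades III–IV | No, read literally | – |
| PFS (death from any cause) | Yes | No |
| OS (death from any cause) | Yes | No |
| Follow-up item on death | Yes, as disease-related or unrelated | No; no category for surgery is named |
| Perioperative complications (collected data) | Probably; no grade limit is stated | Possibly, but this is a data item and not a listed outcome |

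The article does not define the grades. That grade V means death is the standard definition of the scale it names. Grades III–IV are a strict subset of grades III–V, so the stated range can only give the same count or a lower one.

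**How much does one omitted death weigh?**

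If a patient stays in the denominator *n* but is left out of the numerator, the proportion falls by 1/*n*, whatever the number of other complications.

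- Input from *Sample size calculation*: about 100 eligible Dutch patients, of whom about 75% may consent. 100 × 0.75 = 75.
- Overall, with all 75 in the denominator: 1/75 = 0.0133, or about 1.3 percentage points.
- By extent of surgery, the article gives no split. Assuming a subgroup of 40: 1/40 = 2.5 points. Assuming a subgroup of 20: 1/20 = 5.0 points.
- With grade III or higher the patient is counted, and the shift is 0.

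The shift arises only if the patient is not already counted through an earlier grade III or IV complication. The article does not say whether a patient is classified by the worst grade or by any qualifying grade.

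**The case against.** The strongest reply is that the death is recorded elsewhere. It is an event in the primary outcome and in OS. The date of surgery and the perioperative complications are both collected, so a death soon after surgery would be visible and could be tabulated by procedure. Reporting severe non-fatal morbidity beside all-cause mortality is a coherent arrangement. All of this stands, and it keeps the point small. It does not remove it: the article does not describe the outcome as non-fatal, all-cause endpoints do not say that surgery caused the death, and the follow-up item names no such category.

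Four stronger readings are tempting, and the document does not support them.

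- *That the patient would certainly be scored as free of severe complications.* The article does not say how a fatal complication is coded. The exclusion follows from a literal reading of the range and no more.
- *That the outcome is meant to show the harm of more extensive surgery, and that the omission biases the comparison in favour of the procedure with more deaths.* The article gives this outcome no such purpose. *Study objectives* links extent of surgery to PFS, the analyses are mainly descriptive, and stratification by surgery is conditional. Bias would also require deaths to fall unequally between procedures, which nothing in the article indicates.
- *That the adverse event outcome needs grade 5 added.* That outcome reads "treatment-related adverse events associated with systemic therapy or radiotherapy classified according to the Common Terminology Criteria for Adverse Events (CTCAE) version 5.0" and carries no grade limit, so there is no exclusion to correct.
- *That adverse events of adjuvant therapy will go uncollected, because the variable list gives only* "details on administered adjuvant therapy (date, duration and type/regimen of adjuvant therapy". The list is a condensed summary in a journal article, and the full case report form is not shown. Its silence does not show that the fields are absent.

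**Conclusion.** The point holds for the grade range alone. As written, the only listed surgical complication outcome leaves out grade V, and no other listed outcome would identify a death as caused by surgery. The primary outcome and OS are unaffected.

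The practical effect is likely small, because few postoperative deaths are to be expected. Per omitted death it is about 1.3 percentage points overall, if all of about 75 Dutch participants are in the denominator. It is 2.5 to 5 points in a surgical subgroup of 40 to 20, and those sizes are assumptions. Centres outside the Netherlands would enlarge the denominators and shrink these shifts. The conclusion rests on a literal reading of the range and on the standard meaning of grade V.

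**What to change.** In *Primary and secondary outcome*, define severe postoperative complications as Clavien-Dindo grade III or higher (III–V). Report grade V as a separate line as well, by extent of surgery where that stratification is feasible.

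The cost is a change of a few characters in the definition and one extra row in a table. Perioperative complications are already collected with no stated grade limit, so the change probably needs no new data. *Study status* gives recruitment as May 2026 to April 2031, so an amendment early in that period would settle the definition before results accumulate.

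### Less surgical morbidity is part of the hypothesis, but graded surgical harm counts only at Clavien-Dindo III–IV, while CTCAE events of adjuvant therapy have no grade floor

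*Protocol article*

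**What the plan says.** The Introduction sets out the hypothesis that "less extensive surgical management may be associated with similar oncological outcomes while potentially reducing treatment-related morbidity and preserving QoL" and adds: "This registry is designed to explore this hypothesis and generate evidence for future studies".

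The secondary outcomes (Outcomes, Primary and secondary outcome) name two graded harm outcomes, next to each other in one sentence:
- for surgery, "severe postoperative complications (Clavien-Dindo grade III–IV";
- for other treatment, "treatment-related adverse events associated with systemic therapy or radiotherapy classified according to the Common Terminology Criteria for Adverse Events", version 5.0, with no minimum grade.

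The symptom outcome in the same list is tied to the disease, not to its treatment. The section closes by also declaring treatment details and follow-up data to be study outcomes.

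Under Collected variables, the surgical details cover "perioperative findings (dissemination of disease and FIGO stage of disease), and perioperative complications", with no grading scale named there. The follow-up data at 6 months, 2 years and 5 years "include clinical status, symptoms, QoL, evidence of disease recurrence and disease-related or unrelated death". The questionnaires are sent "at the time of diagnosis and during follow-up after 6 months, 2 years and 5 years of diagnosis". The Statistical analysis section plans stratification by extent of surgery, if feasible.

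**The concern.** The argument for less surgery has two parts: similar oncological outcome and less harm. The second part needs a harm outcome that can register what more extensive surgery adds. Some of that added harm may be moderate or may appear late, for example persistent lymphatic problems after node removal. As the outcomes are written, such a problem counts in a graded outcome if it is attributed to radiotherapy. If it is attributed to surgery, it counts only when it is a postoperative complication of grade III or IV.

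Two things are at stake. Staged and unstaged patients could look alike on graded surgical harm because the threshold is high and the events are few. A table that sets graded surgical harm beside graded adjuvant harm would also compare two different thresholds, to the apparent disadvantage of adjuvant therapy.

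**Working it through.** The plan gives no complication rate, event count or power figure on this point, so there is nothing to reproduce. The check is to follow each kind of surgical harm through the outcome and variable lists.

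**Where each kind of harm is counted**
- *Severe postoperative complication (Clavien-Dindo III–IV).* Graded secondary outcome.
- *Postoperative complication below grade III.* Not in the graded outcome. It can be recorded under perioperative complications, for which the article names no scale.
- *Late surgical morbidity of moderate degree.* Not in the Clavien-Dindo III–IV outcome. Not in the CTCAE outcome, which is confined to systemic therapy and radiotherapy. Not naturally a perioperative complication. It can surface through clinical status, symptoms or the questionnaires.
- *Adverse event of systemic therapy or radiotherapy, any grade.* Graded secondary outcome.

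The second and third rows are the gap. It comes from the wording of the outcomes themselves, so a fuller case report form would not change which events count.

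**What the indirect routes can and cannot do**
- After baseline, the first questionnaire comes 6 months after diagnosis, and the longest interval is 5 − 2 = 3 years.
- The questionnaires measure burden. They do not by themselves attribute a symptom to surgery or to adjuvant therapy.
- Adjuvant type, date and duration are recorded, so patients without adjuvant therapy can be described separately. This helps, but it leaves a smaller group.

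**Illustration of size (assumed rates, not from the documents)**

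Assume that 3–5% of staged patients have a severe postoperative complication, that 10–15% have moderate or late surgical morbidity, and that the two groups do not overlap.

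Share captured = severe / (severe + moderate or late)
- lowest: 3 / (3 + 15) = 0.17
- highest: 5 / (5 + 10) = 0.33

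Expected counts: the Sample size section anticipates about 100 eligible Dutch patients with about 75% consenting, so 100 × 0.75 = 75. If half are staged (a further assumption), that is about 37.
- severe: 37 × 0.03 = 1.1 to 37 × 0.05 = 1.9
- moderate or late: 37 × 0.10 = 3.7 to 37 × 0.15 = 5.6

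Under these assumptions the named outcome rests on one or two events among staged patients, and about four to six more fall outside any graded outcome. International centres would raise all the counts but not the share captured.

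**The case against.** The case against has real force on several points.

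- *Surgery is graded.* A reader who takes the CTCAE clause alone might infer that graded adverse events exist only for systemic therapy and radiotherapy. That is wrong: the Clavien-Dindo outcome stands directly before it. Using a surgical scale for surgery is reasonable. What remains is the III–IV floor and the lack of any graded outcome for late surgical morbidity.
- *The registry is not blind to surgical harm.* A reader might conclude that it cannot show the hypothesised benefit. The documents do not support that. Perioperative complications are collected without a grade restriction, symptoms and quality of life are followed to 5 years, treatment details and follow-up data are declared outcomes, and stratification by surgical extent is foreseen. The limit is one of sensitivity and comparability.
- *The follow-up list is not exhaustive.* It uses the word include, and it does not mention CTCAE events either, although these are a named outcome. Absence from that list therefore does not prove that surgical morbidity goes uncollected, and item-level form content may sit in the full protocol. This stands. The point rests on the outcome definition, not on that list.
- *The aims are modest.* The registry is descriptive and exploratory, its association objective concerns progression-free survival, and confounding by indication is acknowledged. This lowers the stakes, but lower morbidity is still part of the hypothesis that the registry says it is designed to explore.
- *Two scales could double count.* Simply removing the restriction on CTCAE would let one surgical event be graded twice. This is correct, and the fix has to prevent it.
- *An earlier questionnaire* after surgery would be a preference, not a correction.

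**Conclusion.** The point holds as a limitation of the outcome definition. Graded surgical harm is restricted to Clavien-Dindo III–IV, and CTCAE grading, which has no floor, is restricted to systemic therapy and radiotherapy. Moderate and late surgical morbidity therefore lies outside every clinician-graded outcome, and graded harms of surgery and adjuvant therapy are not on a comparable threshold. The registry is poorly placed, though not unable, to show the morbidity difference it hypothesises.

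This conclusion rests on the stated outcome wording alone and needs no assumed rate. The 17–33% capture figure and the event counts do depend on assumed rates, on no overlap and on half of the participants being staged. They cover only the named graded surgical outcome and ignore what symptoms, quality of life and ungraded complications may add. They show the order of magnitude only.

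**What to change.** In Primary and secondary outcome:
1. Report postoperative complications of all Clavien-Dindo grades, with III–IV still shown separately.
2. Extend CTCAE v5.0 grading to surgery-related morbidity that arises after the postoperative period, and state where that period ends, so that each event is graded on one scale only.

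Under Collected variables, add to the existing 6-month, 2-year and 5-year forms the type, grade, onset date and attributed treatment of each such event. In the Statistical analysis section, state that these events will be described by extent of surgery.

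The cost is a few minutes of data entry per form. Low-grade events will be reported less completely than severe ones, and the report should say so. No visit, treatment or questionnaire changes. The Study status section gives recruitment as May 2026 to April 2031, so an early change would reach most participants prospectively. Moderate and late harms are hard to reconstruct afterwards.
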